### 3.2.4 Exploratory Efficacy Endpoints

- a) Urine proteomics
- b) Gene expression analysis
- c) DNA sequence analysis

## 4 Trial Design

### 4.1 Overall Trial Design

**Figure 1: Course of the trial**

The duration of conventional treatment of acute cystitis with antibiotics is one to five days, depending on the antibiotic substance. The follow up period of 26 weeks is chosen to analyse frequency of recurrent cystitis.

[figure not shown]

This will be a single center, randomized, open-labeled clinical trial in female subjects with a history of recurrent acute cystitis. The subjects will be randomised to receive either 5 days of Kineret treatment, 100 mg daily as a subcutaneous injection through daily visits at the study clinic or Nitrofurantoin oral antibiotic treatment for 5 days.

### 4.2 Number of Trial Subjects

20 subjects will be treated with Kineret treatment and 10 subjects with Nitrofurantoin. For determination of sample size see section 9.

### 4.3 Subject identification and randomisation of treatment

All enrolled subjects will be randomized 2:1 to two study treatment groups at Visit 1.

#### 4.3.1 Subject identification

Subject screening numbers will be generated sequentially to subjects consenting to participate in the study and used throughout the study as subject identifier (PatientID).

#### 4.3.2 Labelling, randomisation and treatment allocation to the study subject

Approved commercial products (e.g. Kineret and Nitrofurantoin Uro-Tablinen®) are used, which is why labeling according to §5 (8) GCP-V is waived in the context of clinical trials. Unmodified German market goods according to §5 (8) GCP-V are used in this study.

Both drugs, the verum Kineret® and the standard antibiotic Nitrofurantoin, are already approved drugs in the EU. Both are used as commodities in this study and are purchased through the local pharmacy of UKGM Marburg-Giessen. There is no change in either IMP. Patients receiving Nitrofurantoin Uro-Tablinen® will take this drug orally at home on their own twice a day (2x 100 mg). Proper documentation, including accompanying documents, will ensure that the antibiotic Nitrofurantoin is used properly.

Randomization will be performed centrally by the central office of the Center for Clinical Trials of the Philipps-University Marburg.

Randomization will not be possible during public holiday.

Koordinierungszentrum für klinische Studien (KKS)

Philipps-Universität Marburg

[name]

[name]

Monday-Thursday: 8.00 - 16.00 h

Friday: 08.00 - 14.00 h

**E-Mail: [contact]**

*([contact] → if transmission via e-mail is not possible)*

The randomization of an eligible patient can take place if all inclusion criteria and none of the exclusion criteria are fulfilled. Therefore the investigator completes the study specific randomization request form, which is part of the Investigator Site File (ISF) and sends it to the KKS Marburg via e-mail (preferably) or fax.

The chance for allocation to the verum group or control group is 2:1.

KKS Marburg will report the randomization result.

Patients randomized to Kineret will be allocated 5 vials with investigational product. Patients randomized to antibiotics will receive treatment for 5 days.

Since this is an open study the administrated Investigational product will be documented together with date, time and study code in the source documentation and eCRF.

## **5 Trial Population and Withdrawal**

### **5.1 Subject Eligibility**

The (sub)investigator should only enrol subjects who meet all eligibility criteria, are not put at undue risk by participating in the trial and can be expected to comply with the protocol.

The subject's eligibility for the clinical trial must be checked according to the inclusion and exclusion criteria as specified below in section 5.2. and 5.3. See also "Schedule of Trial Procedures" ( section 6.1).

### **5.2 Inclusion Criteria for All Subjects**

1. Stable patients with an acute episode of recurrent uncomplicated cystitis.
2. Signed written informed consent form
3. Capability and willingness to comply with study procedures
4. Female subjects, 18 - 65 years old
5. Negative urine pregnancy test in women of childbearing potential.
6. Sum score of the main uUTI symptoms reported on the Acute Cystitis Symptom Score (ACSS) typical domain at visit 1 is  $\geq 6$
7. Typical symptoms must be acute, developed within  $\leq 6$  days
8. Historys of recurrent cystitis ( $\geq 3$  documented episodes in the history in the past year) or ( $\geq 2$  documented episodes in the history in the past 6 months))
9. Contraception

Contraception should be maintained during treatment and 30 days after last intake. Women of childbearing potential must use contraceptive methods which are considered as highly effective birth control methods. Such methods include:

- combined (estrogen and progestogen containing) hormonal contraception associated with inhibition of ovulation:
  - oral
  - intravaginal
  - transdermal

- progestogen-only hormonal contraception associated with inhibition of ovulation:
  - oral
  - injectable
  - implantable
- intrauterine device (IUD)
- intrauterine hormone-releasing system ( IUS)
- bilateral tubal occlusion
- vasectomised partner
- sexual abstinence

Hormonal contraception methods should be combined with barrier methods.

### 5.3 Exclusion Criteria for All Subjects

1. Breastfeeding
2. Signs of pyelonephritis
3. Uncontrolled Diabetes Mellitus
4. Neutropenia ( $<1,5 \times 10^9/L$ )
5. Signs of genital infections (Vaginitis/ cervicitis)
6. Anamnestic exclusion of patients with active severe infections, history of viral hepatitis (only anamnestic exclusion possible, as immediate inclusion in the study is urgently required for this disease pattern. Serological and other blood test results (processing time  $\geq 24$  hours) cannot be waited for).
7. Patients using CYP450 medications (e.g. Warfarin, Phenytoin)
8. Patients using Phenytoin medication
9. Anamnestic exclusion of patients with a history of tuberculosis or active tuberculosis (only anamnestic exclusion possible, as immediate inclusion in the study is urgently required for this disease pattern. Serological blood test results (processing time  $\geq 24$  hours) cannot be waited for)
10. Extragenital conditions, nephrological conditions, urological conditions, urinary catheters that may lead to complicated UTI
11. Severe uncontrolled systemic disease
12. Systemic Antibiotic therapy within 5 days prior to inclusion
13. Impaired renal function (Creatinine clearance  $< 60$  ml /min)

14. Known allergies/contraindications to Kineret and Nitrofurantoin
15. Malign diseases
16. Immunosuppression
17. Previously enrolled in this trial
18. Pathological liver enzymes
19. Polyneuropathies
20. Glucose-6-phosphate dehydrogenase deficiency
21. Participation in other interventional clinical trials
22. Use of Diclofenac and Ibuprofen analgetic medication while participating in this clinical trial

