#### 3.2.2 Safety Endpoints

Change in laboratory safety variables, vital signs, physical examination from baseline and the incidence of adverse events, treatment emergent adverse events, serious adverse events during the trial.

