| Patients                                                                                         | All patients         | All patients      | Only patients of
Kineret® Arm       | All patients               | All patients         | All patients               | All patients       |
| Dispensing of Study
Medication (Patient
randomised to Kineret®)                            | X                    | X                 | X                                      |                            |                      |                            |                    |
| Dispensing of study
medication
(Patient randomised to
Nitrofurantoin Uro-
Tablinen®) | X                    |                   |                                        |                            |                      |                            |                    |
| Adverse Event(s)                                                                                 | X                    | X                 | X                                      | X                          | X                    | X                          | X                  |
| Vital signs                                                                                      | X                    | X                 | X                                      | X                          |                      | X                          | X                  |
| Blood sample
(haematology)                                                                    | X                    | X                 | On Visit 3: only
WBC & differential | Only WBC &
differential |                      | Only WBC &
differential | X                  |
| Blood sample
(biochemistry)                                                                   | X                    | X                 |                                        |                            |                      |                            | X                  |
| Urine RNA                                                                                        | X                    | X                 |                                        | X                          |                      | X                          | X                  |

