## 6.10 Laboratory Assessments

### 6.10.1 Safety Blood Tests (hematology, biochemistry)

Samples for analysis of parameters must be taken according to the schedule of trial procedures (section 6.1) or on withdrawal from or early completion of the treatment phase of the clinical trial.

| The following analyses will be performed on the venipunctured blood samples: | Parameter                                                                                                                                                                 |
|------------------------------------------------------------------------------|---------------------------------------------------------------------------------------------------------------------------------------------------------------------------|
| Haematology                                                                  | Haemoglobin
Haematocrit
Red blood cell (RBC) count
Mean corpuscular volume (MCV)
White blood cell (WBC) count, including differential count
Platelet count |
| Biochemistry (serum/plasma)                                                  | Urea
Creatinine
Sodium
Potassium
Glucose                                                                                                                      |

If any laboratory results are abnormal, the investigator should follow-up the subject as clinically appropriate.

Routine analyses of blood samples (clinical chemistry) will be processed at the central laboratory of the university hospital Giessen-Marburg, location Giessen. At the end of the clinical trial, parts of the samples are shipped to the local laboratory at the Lund University, Sweden. Handling and shipment instructions are provided in laboratory manuals by the laboratory at the Lund University.

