**Table 1: List of adverse drug reactions associated with Kineret®**

| System Organ Class                    | Preferred term ordered by seriousness                                                    | Frequency |
|---------------------------------------|------------------------------------------------------------------------------------------|-----------|
| Infections and parasitic diseases     | Serious infections                                                                       | ≥ 1/100   |
| Blood and the lymphatic system        | Neutropenia                                                                              | ≥ 1/100   |
| Blood and the lymphatic system        | Trombocytopenia                                                                          | ≥ 1/100   |
| Immune system                         | Allergic reactions, including anaphylactic reactions, Angioedema, Urticaria and Pruritus | ≥ 1/1000  |
| Central and peripheral nervous system | Headache                                                                                 | ≥ 1/10    |
| Liver and Bile                        | Increased liver enzymes                                                                  | ≥ 1/1000  |
| Liver and Bile                        | Non-infectious hepatitis                                                                 | Not known |
| Skin and subcutaneous                 | Injection-site reaction                                                                  | ≥ 1/10    |
| Skin and subcutaneous                 | Rash                                                                                     | ≥ 1/1000  |
| Blood assessments                     | Increased cholesterol                                                                    | ≥ 1/10    |

**Please note that data on adverse reactions/adverse events may change over the time. For that reason, it is necessary that the investigator is familiar with the current version of the SmPC which is filed in the Investigator site file (ISF).**

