## 11 Administration

### 11.1 Source data and patient files

The investigator has to keep a written or electronic patient file for every patient participating in the clinical study. In this file, the available demographic and medical information of a patient has to be documented, in particular the following: name, year of birth, sex, height, weight, patient history, concomitant diseases and concomitant drug (including changes during the study), study identification, patient number, the date and process of informed consent, all study visit dates, predefined performed examinations and clinical findings, observed AEs and reason for withdrawal from the study if applicable. It should be possible to verify the inclusion and exclusion criteria for the study from the available data in this file and to identify each subject based on their patient file. All original printouts generated by technical equipment must also be archived as source data. All these documents must bear at least the patient identification and the print date printed out by the recording device in order to be able to assign them reliably. The printouts must be medically evaluated, dated and signed by the investigator.

For all data recorded, the source document must be defined in a source data agreement list at the trial site. There must only be one source defined at any time for any data elements. The list must be signed by the investigator and the CRA prior to trial start.

The trial monitor will check the eCRFs for accuracy and completeness by verifying data recorded in the CRF against source data to ensure such records are consistent.

Source data should, as a general rule be recorded in the subject's medical record or other defined document normally used at the trial site. Source data not normally collected as a routine part of the clinical practice at the site may be entered on a worksheet. Clinical assessments/safety evaluations must be signed by medically qualified (sub)investigators.

If the worksheet does not become part of the subject's medical record, the following should as a minimum be added to the subject's medical record:

For this clinical trial, the following parameters collected in the eCRF should be verifiable from source documents available at the trial site:

- Date of trial visits and date leaving the clinical trial
- Relevant medical history and diagnosis
- Nature of contraception used by the subject and result of pregnancy test(s), when applicable

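### Exclusion 18 is worded as a liver-enzyme result, but the protocol sets no limit and schedules no liver test, at entry or on treatment

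*Protocol*

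**What the plan says.** Exclusion no. 18 in Protocol 5.3, repeated in the Synopsis, reads "Pathological liver enzymes". It gives no enzyme, limit or source of information. Nos. 6 and 9 in the same list, on infection and viral hepatitis and on tuberculosis, are expressly limited to history: "only anamnestic exclusion possible, as immediate inclusion in the study is urgently required for this disease pattern".

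Section 6.10.1 lists the blood tests. Haematology has six items. Biochemistry has five: "Urea Creatinine Sodium Potassium Glucose". The schedule in 6.1 draws biochemistry at Visits 1, 2 and 5 and at unscheduled visits. Scheduled safety blood at Visits 6 and 7 is white cells and differential only. None of the visit lists in 6.2 adds a liver test.

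Sections 4.3.2 and 5.1 allow randomisation only when every criterion has been checked and no exclusion applies. Section 11.1 says of the patient file: "It should be possible to verify the inclusion and exclusion criteria for the study from the available data in this file". The safety endpoints in 3.2.2 include "Change in laboratory safety variables, vital signs, physical examination from baseline". Table 1 in 8.2.2 lists "Increased liver enzymes" for Kineret at 1/1000 or more. The corresponding table in 8.4.2 gives the same floor for nitrofurantoin, in a row that pools cholestasis, hepatitis and raised transaminases.

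**The concern.** Three exclusions are worded as blood results: neutropenia (no. 4), creatinine clearance (no. 13) and liver enzymes (no. 18). The Visit 1 panel supplies an analyte for the first two and none for the third. Trial procedures therefore put nothing into the file against which no. 18 could be verified.

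Two things are at stake. At entry, a patient with an unrecognised abnormality can be randomised to a drug with a listed liver effect, although the protocol means to keep her out. On treatment, a rise without symptoms goes unmeasured. It then appears neither in the laboratory tables nor as an adverse event, although Appendix 1 requires clinically significant laboratory abnormalities to be recorded as adverse events.

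The criterion also bears on the analysis. Section 9.2 restricts the full analysis set to enrolled subjects who meet the eligibility criteria and cuts the safety set from it. A criterion that is neither defined nor measured thus helps to decide who is analysed.

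**Working it through.** The protocol gives no figure of its own here to reproduce. The check sets the sections side by side and then gauges the scale.

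**1. Panel against criterion.** Section 6.10.1 lists 6 haematology + 5 biochemistry = 11 analytes. Liver enzymes among them: 0 of 11. Scheduled biochemistry samples: 30 patients × 3 visits (1, 2, 5) = 90, none of which measures a liver enzyme. Alkaline phosphatase appears in the abbreviation list but in no panel or visit.

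**2. Exclusions worded as a blood result.**

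| Exclusion | Limit stated | Analyte at Visit 1 |
|---|---|---|
| No. 4, neutropenia | yes, below 1.5 × 10⁹/L | yes, differential count |
| No. 13, creatinine clearance | yes, below 60 ml/min | yes, creatinine |
| No. 18, liver enzymes | no | no |

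**3. Chance of at least one enzyme rise on treatment.** Formula: P = 1 − (1 − p)^n. With p = 1/1000, the floor in both adverse reaction tables:

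- Kineret, n = 20: 1 − 0.999^20 = 2.0%
- Nitrofurantoin, n = 10: 1 − 0.999^10 = 1.0%
- Both arms, n = 30: 1 − 0.999^30 = 3.0%

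The tables state a floor and no ceiling. If p were 1/100, which is an assumption and not a protocol figure, the result for n = 30 would be 1 − 0.99^30 = 26.0%. Whatever p is, the planned panel detects none of the rises that stay silent.

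**4. What testing could say about rates.** With no events in n patients, the one-sided 95% upper limit is 1 − 0.05^(1/n): 13.9% for 0/20 and 25.9% for 0/10. Testing would therefore serve eligibility and individual safety. It would not give a useful comparison of hepatic event rates.

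**5. Prevalence at entry.** The protocol gives no frequency of unrecognised liver-enzyme abnormality in this population, so no figure is offered.

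**The case against.** The strongest case against is that this is a short course of two approved drugs with an infrequent listed effect, and that the panel is deliberately selective. Raised cholesterol is listed for Kineret at 1/10 or more and is not measured either, while neutrophils are followed closely. Section 5.1 obliges the investigator to check every criterion and to enrol nobody at undue risk. Earlier results and the history taken under 6.6 can support that check, and nothing forbids ordering a liver test. Section 9.3.1 classes a value above the reference range as high, which is a natural reading of pathological. Symptomatic liver injury would still surface as an adverse event or at an unscheduled visit, where further assessments are allowed.

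Most of this stands and limits the point. It does not remove it, because no section requires the test on which no. 18 depends. Several stronger readings are tempting, and the documents do not support them:

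- **That only an already known abnormality can exclude a patient.** The protocol does not require a test, but it does not prevent one.
- **That the missing history-only wording proves a test was intended.** Nos. 15, 16, 19 and 20 (malignancy, immunosuppression, polyneuropathy, enzyme deficiency) also lack both that wording and a scheduled test.
- **That the expected yield is 2% to 3%.** The listed frequencies are floors. The text above the nitrofurantoin table also calls the effects rare, which conflicts with the liver row.
- **That the listed nitrofurantoin frequencies can be scaled by a dose ratio.** They refer to 30 mg three times daily, while the trial dose is described both as 2 × 100 mg and as 3.6 mg/kg daily. No single ratio follows.
- **That 8.4.9 already requires liver monitoring.** That sentence concerns the management of toxicity and attaches no test or visit.

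**Conclusion.** The point holds in this form: no. 18 is worded as a laboratory result without a limit, and the protocol requires no liver test at any visit. At entry, detection depends on existing records or on a test ordered outside the protocol. On treatment, a silent rise cannot reach the laboratory safety endpoint.

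The measurable size is modest: about a 3% chance of at least one rise among 30 patients at the listed floor, assuming independent patients and p = 1/1000 in both arms. The true figure is unknown. The gap does not invalidate the trial or touch the primary endpoint. It is worth correcting because the correction is cheap and makes the criterion checkable. The panel and the eligibility criteria are fixed in the protocol and are not matters for a statistical analysis plan.

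**What to change.** 1. **Measure.** Add ALT and AST, optionally ALP and bilirubin, to the biochemistry sample already drawn at Visits 1, 2 and 5 (6.1, 6.10.1). Preferably add them to the blood taken at Visit 6 as well. Section 9.3.1 already plans a biochemistry change to Visit 6, while the schedule provides no biochemistry then. A Visit 6 value would also show a rise that appears after the last dose.
2. **Define.** Give no. 18 a limit, for example ALT or AST above a sponsor-chosen multiple of the laboratory's upper reference limit.
3. **Use one eligibility rule for everyone**, so that laboratory timing does not decide who is enrolled. Either (a) wait for the same-day Visit 1 result before randomisation, or (b) if that is not feasible, reword no. 18 as known or anamnestic, like nos. 6 and 9. Under (b) the Visit 1 result serves only as a safety baseline and for a continue-or-stop decision under 5.6.1, by telephone for nitrofurantoin patients on Days 3 and 4. The protocol says of chemistry that "Routine analyses of blood samples (clinical chemistry) will be processed at the central laboratory of the university hospital" but gives no turnaround time, so the site must settle which option is workable.
4. **Protect the analysis sets.** Amend 9.2 so that every treated patient stays in the safety set, and a late abnormal Visit 1 value does not remove a randomised patient from the full analysis set.

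**Cost.** Two assays × 3 visits × 30 patients = 180, or 240 with Visit 6. Four assays give 360, or 480 with Visit 6. Add eCRF fields and an amendment. There is no extra visit. Option (a) may delay randomisation, since the central office closes at 16.00 (14.00 on Fridays); option (b) adds no wait. An occasional early stop is possible, and one patient is 1 of 20 on Kineret or 1 of 10 on nitrofurantoin. Under 5.6.1 evaluations continue on schedule, so the Day 5 symptom score should still be collected, but it would reflect a part course plus any replacement therapy.

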Clinical Trial Protocol

Interest in the use of anti-inflammatory drugs has increased in recent years, mainly in the form of NSAIDs, as an alternative to antibiotic therapy for uncomplicated cystitis with varying results [6]. The studies show that NSAIDs can be useful for treatments of acute symptoms and may slightly decrease recurrent cystitis, but due to a lack of specificity, these anti-inflammatory agents cannot completely replace antibiotics in the treatment of acute cystitis [7-9]. We believe that our strategy, to block the IL-1 receptor, has a much more precise and well-defined molecular mechanism as well as extensive support in experimental models.

Based on the research results described above, we want to evaluate the possibility of treating recurrent acute cystitis with Kineret. We want to investigate whether the treatment provides adequate cure for acute cystitis compared to conventional antibiotic treatment, both based on the patient's symptoms and inflammation and on the effects on bacteria in the urine.

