## **6.7 Concomitant Medication**

At each study visit/contact, the investigator should question the subject about any medication taken by the subject.

All concomitant medication, with the exception of vitamins and/or dietary supplements, administered during the time period from randomisation to last administration of study drug, are to be recorded in the eCRF. This also applies to concomitant medication administered prophylactically in anticipation of reaction to the active treatment and any medication intended to treat an AE.

A prophylactic medication is a medication administered in the absence of ANY symptom and in anticipation of a reaction to the active treatment (e.g. an anti-pyretic, corticosteroids, etc.).

Similarly, concomitant medication administered for the treatment of a SAE at any time, must be recorded on the SAE Report as applicable.

Use of non-marketed/other investigational products one month prior to Visit 1 and during the trial is not permitted.

Refer to Appendix 2 for the definition of a SAE and to Section 7.7 for the applicable reporting periods and required information.

Use of concomitant treatment must be recorded in the subject's medical record and the eCRF detailing treatment/drug name, dose, indication and dates of start and stop.

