## 8.2 Manufacturing, packaging and labelling of Kineret®

Kineret® is administered by subcutaneous injection. The Kineret® is ready for use in a graduated pre-filled syringe. The graduated pre-filled syringe allows doses between 20 and 100 mg. Because the minimum dose is 20 mg, the syringe is not

suitable for pediatric patients with a body weight below 10 kg. Do not shake the pre-filled syringe. For instructions on use and handling, see Sustainability, Storage and Handling.

It is recommended that the injection site be varied to avoid discomfort at the injection site. Cooling of the injection site, heating the injection fluid to room temperature, use of a cooling pack (before and after injection) and use of topical glucocorticoids and post-injection antihistamines can alleviate signs and symptoms of injection site reactions.

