## 9.2 Definition of Trial Analysis Sets

All subjects enrolled in the trial (i.e. subjects for whom informed consent has been obtained) will be accounted for in the clinical trial report.

A full analysis set will comprise all enrolled subjects who meet the protocol-defined eligibility criteria.

A safety analysis set will be defined by excluding subjects from the full analysis set who either received no treatment with investigational product and/or for whom no post-baseline safety evaluations are available.

The decisions regarding inclusion/exclusion of subjects and/or subject data from the trial analysis sets will be documented in the clinical trial report.

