## ACSS-Fragebogen

## Kontrollvorstellung (Folgebefund) – Teil B

Uhrzeit: \_\_\_\_ UU: \_\_\_\_ MM Datum der Untersuchung: \_\_\_\_ / \_\_\_\_ / \_\_\_\_ (Tag/Monat/Jahr)

Bitte geben Sie an, ob Sie irgendwelche Änderungen in Ihrem Zustand seit dem Ausfüllen des ersten Teils unseres Fragebogens bemerkt haben? (kreuzen Sie bitte Ihre Antwort an):

- Dynamik**
- ☐ 0 Ich fühle mich jetzt ausgezeichnet (alle Symptome sind endgültig vergangen)
- ☐ 1 Mir geht es jetzt wesentlich besser (die Mehrheit der Symptome sind vergangen)
- ☐ 2 Ich fühle mich jetzt nur gering besser (die Mehrheit der Symptome sind immer noch da)
- ☐ 3 Es gibt jetzt keine Änderung meines Zustands (alle Symptome sind noch vorhanden)
- ☐ 4 Es ist jetzt schlimmer geworden (mein Zustand hat sich verschlechtert)

Bitte geben Sie an, ob Sie unten genannte Symptome innerhalb der letzten 24 Stunden bemerkt haben, und bewerten Sie bitte deren Intensität (nur eine Antwort für jedes einzelne Symptom):

|                                   |                                                                                                                                                                                                                                                                           | 0                                                                                                                                                                                                                                                                                                                                                                                                                           | 1                                                                               | 2                                                                        | 3                                                                |

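### Exclusion criterion 22 is an on-study drug restriction filed as an eligibility criterion and limited to two NSAIDs, so analysis-set membership and the Day 5 ACSS can both depend on symptomatic drug use

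*Protocol*

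**What the plan says.** Item 22 of Protocol section 5.3 reads "Use of Diclofenac and Ibuprofen analgetic medication while participating in this clinical trial", and the synopsis repeats it. It is the only rule in the protocol written about analgesic or anti-inflammatory co-medication.

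Section 2.1 speaks of the class: "The studies show that NSAIDs can be useful for treatments of acute symptoms and may slightly decrease recurrent cystitis". The same paragraph describes the results as mixed.

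Section 6.7 has the investigator ask about any medication at each contact. Its main recording sentence covers medication "administered during the time period from randomisation to last administration of study drug, are to be recorded in the eCRF". It includes prophylactic drugs, defined as those given "in anticipation of a reaction to the active treatment (e.g. an anti-pyretic, corticosteroids, etc". Its only prohibition is "Use of non-marketed/other investigational products one month prior to Visit 1 and during the trial is not permitted". Sections 8.3.5 and 8.4.11, on allowed concomitant medication, deal with interactions and, in 8.4.11, with treatment of anaphylaxis. Neither sets a rule on symptomatic drugs.

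Section 9.2 states: "A full analysis set will comprise all enrolled subjects who meet the protocol-defined eligibility criteria". The primary endpoint (3.2.1) is the reduction in ACSS over the first five days. During treatment the questionnaire is completed only at Visit 1 and on Day 5. Its symptom items carry a 24-hour recall: "Bitte geben Sie an, ob Sie unten genannte Symptome innerhalb der letzten 24 Stunden bemerkt haben". The trial is open label, with 20 patients on Kineret and 10 on Nitrofurantoin.

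**The concern.** A criterion about behaviour during the trial cannot be verified when eligibility is checked. It can only be failed later, and the analysis-set definition refers back to it. Taking a painkiller is plausibly related to how well the bladder symptoms are resolving, so a rule that removes patients for doing so selects on something close to the outcome.

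The rule is also narrow. A patient who takes a symptom-relieving drug other than the two named breaks no written rule. She contributes a Day 5 score in which the effects of study drug and analgesic cannot be separated.

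At stake is the reading of a patient-reported score in a small trial where both patient and investigator know the allocation.

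**Working it through.** The plan gives no figure for analgesic use or its effect, and no effect size or SD for the ACSS change, so there is nothing of its own to reproduce. The check is mainly a comparison of passages.

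**1. When the rule can be applied.** The schedule in 6.1 places the eligibility check at Visit 1 only. Item 22 concerns use while participating, which runs to week 26. The mandatory reasons for stopping treatment in 5.6.1 include nothing that corresponds to it.

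**2. What follows under 9.2.** The full analysis set requires the eligibility criteria to be met, and item 22 is one of them. Taken at its word, ibuprofen on Day 3 or in week 20 means a criterion is no longer met. Because 9.2 forms the safety set by removing patients from the full analysis set, that patient would leave the safety set too. Each such patient weighs:

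- Nitrofurantoin arm: 1/10 = 10%
- Kineret arm: 1/20 = 5%

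**3. What is left uncontrolled.** Section 2.1 speaks of NSAIDs in general; item 22 names two. Sections 6.7, 8.3.5 and 8.4.11 add no restriction on symptomatic drugs. Item 7 (CYP450 medications, an undefined class) and item 16 (immunosuppression) may bar some drugs at entry, but neither is written to control symptom relief.

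**4. Recording period.**

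| Source | Period |
|---|---|
| Item 22 | all of participation |
| 6.7, main eCRF sentence | randomisation to last dose |
| 6.7, opening and closing sentences | each visit or contact; eCRF entry with start and stop dates |
| Schedule, 6.1 | every visit, the Day 30 call and unscheduled visits |

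These do not agree. On the narrow sentence, a breach of item 22 in follow-up need not reach the eCRF, nor need a drug stopped before randomisation but inside the 24 hours recalled by the Day 1 ACSS.

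**5. Illustration on assumed inputs.** Let a share p of an arm take a reliever that lowers the score by b standard deviations (SD) of the change. Neither p nor b is in the protocol.

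*Between arms:* shift = (difference in p) × b.

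- Difference 0.20, b = 0.5 to 1.5: 0.10 to 0.30 SD
- Difference 0.40, b = 0.5 to 1.5: 0.20 to 0.60 SD

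*Within an arm:* section 9.3 names a one-tailed paired t-test of no change at alpha 0.05. With no study-drug effect, the noncentrality is √n × p·b / √(1 + p(1−p)b²). For n = 20, p = 0.2, b = 0.5 this is √20 × 0.10/√1.04 = 0.44. Rejection probabilities over b = 0.5 to 1.5, against a nominal 0.05:

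| p | n = 20 | n = 10 |
|---|---|---|
| 0.2 | 0.11 to 0.30 | 0.09 to 0.19 |
| 0.4 | 0.21 to 0.67 | 0.14 to 0.41 |

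This shows only that co-medication feeds into the stated test even when both arms use it equally. It does not estimate what will happen.

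**The case against.** The strongest reply is that item 22 will be handled sensibly. Section 5.1 ties eligibility to whom the investigator enrols. Section 9.2 does not say that later conduct revokes membership, and leaves inclusion decisions to be documented in the trial report. Section 11.4 has every violation recorded, tracked and reviewed before soft lock for its effect on efficacy. This stands to the extent that dropping users is one literal reading and not a stated instruction. But nothing says which route applies to item 22, and the literal one should not be available.

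Four stronger readings are tempting and not supported:

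- **That other analgesics, antipyretics or corticosteroids are expressly permitted.** Section 6.7 is a recording rule and a definition. The drugs are not prohibited, which is less than being allowed. The remark in 8.2 that "use of topical glucocorticoids and post-injection antihistamines can alleviate signs and symptoms of injection site reactions" concerns the injection site; nothing links it to bladder symptoms.
- **That analgesic use must be higher on Kineret because of headache.** The tables in section 8 list headache at ≥1/10 for both drugs, and drug fever at ≥1/10 for Nitrofurantoin. Injection-site reactions and knowledge of the arm remain as arm-specific reasons, but they do not fix a direction.
- **That a baseline lowered by a painkiller would be invisible.** Visit 1 asks about concomitant medication, and 6.7 also calls for start and stop dates. Such use is documentable, though eCRF entry is not assured. Use before randomisation is balanced between arms in expectation.
- **That item 22 contradicts section 2.1.** That section is hedged. Naming two NSAIDs is narrower than the class statement, not incompatible with it.

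The endpoint definition names no ACSS domain, and the questionnaire's separate change item refers back to the first questionnaire. The 24-hour argument applies to the symptom items.

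Finally, how Day 5 scores are analysed after analgesic use is ordinary SAP content, and its absence here is no gap. A SAP cannot, however, create a conduct rule or recover data that the eCRF did not require.

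**Conclusion.** The point holds as a defect of placement, scope and recording. Item 22 is a post-randomisation restriction listed as an eligibility criterion, it covers two named drugs only, and it is not carried into the concomitant-medication sections. Through 9.2 it permits removal of randomised patients for an act that may be related to outcome. Users of other symptomatic drugs stay in with a Day 5 score that may be lowered by them.

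The firm size is 10% of the Nitrofurantoin arm or 5% of the Kineret arm per patient removed. Any effect on the arm difference or the within-arm test depends on assumed use and effect, so its direction and magnitude are unknown. A reader might infer that the Day 5 result will favour one arm; the protocol does not support that. The change should be made because it is cheap and protects a small open-label comparison, not because bias has been shown.

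**What to change.** 1. Move item 22 from section 5.3 and the synopsis into section 6.7 as an on-study restriction. Use then becomes a recorded deviation under 11.4. State in 9.2 that users remain in the full analysis set.
2. Reconcile item 22, section 2.1 and section 6.7 into one statement of which symptomatic drugs are restricted and for what period, identical in both arms. The sponsor decides the content.
3. Align the recording window in 6.7 with the schedule and with the restriction period. Add an eCRF item for any symptomatic drug taken in the 24 hours before the Day 1 and Day 5 ACSS.

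A sensitivity analysis for Day 5 users can be left to the SAP. No particular imputation is proposed here.

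The cost is protocol wording and one small eCRF item at two existing visits.
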